### 6.3 Follow-up period

The follow-up period will start at the 4-week visit and will last until 3 months after start of IMP intake. During the follow-up period, information on health care services that the subjects have received in public health care is collected from the Care Register for Health Care, and information on possible deaths is collected from death certificates archived by Statistics Finland.

At 3 months after the start of IMP intake, all subjects will be contacted by telephone for an interview on possible AEs and concomitant medications. This telephone contact will conclude the study participation.

After the follow-up period, with the subject's consent, additional post-study follow-up information will be collected from the Care Register for Health Care and from death certificates archived by Statistics Finland until 6 months after start of IMP intake.

## 7 ASSESSMENTS

### 7.1 Screening data

#### 7.1.1 Demographic and other baseline information

Information to be recorded during the screening visit includes:

- subject's name, personal identity number, address (only for use at the site; not to be entered into the electronic case report forms (eCRF));
- ethnic origin;
- habits (for the use of nicotine, alcohol, illicit drugs, special diets);
- vital signs (seated or supine blood pressure and heart rate after 10 min rest, tympanic body temperature, respiratory rate, SpO2);
- 12-lead ECG results;
- results of the physical examination, including body height and weight and chest auscultation findings;
- answers to the GAD-7 questionnaire;
- information on symptoms of Covid-19 infection and possible exposure to the SARS-CoV-2 virus;
- information on previous diseases; the screening interview includes a review of the subject's mental health status, with particular attention to suicidal behaviour and suicide attempts in the past five years;
- information on previous medications; prescription medications 4 weeks before the screening visit will be recorded; over the counter medications, herbal

remedies, trace elements, vitamins, within 4 weeks before the screening visit will be recorded;

- information on previous participation in clinical trials;
- name and information of the subject's next-of-kin (not into eCRF; this information will be removed from the subject's source data after the study).

#### 7.1.2 Screening laboratory safety determinations

Screening laboratory safety assessments include:

- P-Alanine aminotransferase (ALT)
- P-Aspartate aminotransferase (AST)
- P-Bilirubin, total
- P-Creatinine
- Glomerular filtration ratio (eGFR), estimated (based on CKD-EPI equation)
- C-reactive protein (CRP)
- Complete blood count

#### 7.1.3 Covid-19 related laboratory assessments

Covid-19 related laboratory assessments include:

- result(s) of SARS-CoV-2 PCR analysis of nasopharyngeal swab sample(s)
- sample collection for analysis of SARS-CoV-2 antibodies in serum
- sample collection for analysis of other Covid-19-related biomarkers (e.g. P-Ferritin, P-FIDD, P-IL6) in serum or plasma samples.

### 7.2 Assessment of efficacy

#### 7.2.1 Evaluation of patient records

The patient records will be evaluated, including information collected from health-related registers (the Care Register for Health Care and death certificates archived by Statistics Finland), until 6 months after start of IMP intake to determine the following endpoints:

- number of hospitalizations due to Covid-19 infection within four weeks of entry into the study;
- number of Intensive Care Unit treatment episodes due to Covid-19 infection within four weeks of entry into the study;
- number of deaths due to Covid-19 infection within four weeks of entry into the study;
- number of hospitalizations due to Covid-19 infection within three months of entry into the study;
- number of Intensive Care Unit treatment episodes due to Covid-19 infection within three months of entry into the study;
- number of deaths due to Covid-19 infection within three months of entry into the study;
- all-cause mortality within six months of entry into the study including post-study follow-up of consenting participants);
- all-cause hospitalizations within six months of entry into the study (including post-study follow-up of consenting participants).

### 7.2.2 Patient-reported health outcomes

During the first two weeks of the treatment period, the subjects are asked to report their symptoms (including body temperature and SpO2) in the form of daily self-assessments, in order to determine the following endpoint of the study:

- duration and severity of Covid-19-related symptoms.

In addition, the mental health and well-being of the participants will be monitored by asking them to complete the GAD-7 questionnaire at the screening visit and at the 2- and 4-week visits. The script of the daily telephone interviews includes questions on possible suicidal ideation and impairment of mental health. Should the answers to these questions reveal significant adverse changes from baseline or an elevated risk for self-harm, the investigator will be informed, and will then take the necessary actions to provide appropriate psychiatric evaluation and care for the subject, without delay.

### 7.2.3 SARS-CoV-2 PCR analysis

Nasopharyngeal swab samples are collected for SARS-CoV-2 PCR analysis at the screening visit (unless a previous positive test result is available) and the 2- and 4-week visits, in order to determine the following exploratory endpoint of the study:

- extent and duration of SARS-CoV-2 viral shedding.

### 7.2.4 Analysis of antibodies and biomarkers

Serum and plasma samples are collected for analysis of SARS-CoV-2 antibodies and other Covid-19-related biomarkers (e.g. P-Ferritin, P-FIDD, P-IL6) at the screening and the 2- and 4-week visits, in order to determine the following exploratory endpoints of the study:

- extent and time course of SARS-CoV-2 virus-specific antibody responses in serum;
- possible other biomarker changes in blood in study subjects.

## 7.3 Assessment of safety

### 7.3.1 Clinical safety assessments

During the treatment period, body temperature and SpO2 will be measured at the 2-week visit.

### 7.3.2 Laboratory safety assessments

Please refer to Section 7.1.2 for laboratory safety assessments to be performed during the screening visit. The same laboratory assessments will be repeated at the 2-week and 4-week visits, in addition to sample collection for later biomarker and HCQ concentration analysis.

### 7.3.3 Adverse events

AEs will be collected from informed consent until the end of the follow-up period. During the study visits, the subjects are asked about AEs with non-leading questions. Outside of the visits, daily telephone contact will be maintained with all subjects who have symptoms, and all subjects are instructed to contact the study personnel if they experience a serious or significant AE, if their condition worsens or if they are hospitalized for any reason during the treatment period. In case of minor AEs, the subjects are to report them on their next visit to the study site or during their next telephone contact.

Definitions of adverse events (AE) and serious adverse events (SAE) and the documentation and reporting of them within this study follow GCP, EU and Finnish national guidance.

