Study participation consists of two phases: a treatment period and a follow-up period. Possibly eligible persons who contact the study sites to seek medical advice and treatment for possible Covid-19 infection will be informed about the study. A screening visit will be scheduled for possibly eligible subject candidates. At this visit, informed consent will be recorded in writing, and subject candidates will be evaluated for eligibility. Subjects may be enrolled and randomized, and treatment with study drugs may be started once the results of the screening assessments are available. A positive test result in SARS-CoV-2 PCR analysis of a nasopharyngeal swab sample taken and analysed outside of this study may be used for evaluation of virus positivity, if taken within five days of enrolment. Enrolment of subjects without previous PCR-confirmed SARS-CoV-2 virus shedding must have to await a positive SARS-CoV-2 PCR test result of a nasopharyngeal swab sample collected at the screening visit. Enrolment and randomization will be performed and IMP will be dispensed and delivered to study subjects only after the investigator has confirmed the subject's eligibility.

During the treatment period, all participating patients will receive standard care for their Covid-19 infection, according to local treatment practice, which includes daily telephone contacts for evaluation of symptoms. In addition, they will receive study medication to take at home, 300 mg of HCQ to be taken twice daily on the first day, and then 200 mg b.i.d. for six days (Days 2-7), or corresponding placebo capsules. On Day 8, they will be contacted by telephone for an interview on symptoms and possible AEs. Approximately 2 weeks and 4 weeks after start of drug intake, the subjects will visit their study site for assessments. The participants will be instructed to contact the study site at any time during the treatment period if their condition worsens, if they experience a serious or significant AE or if they are hospitalized for any reason. The subjects will be provided with a participant card containing study-related instructions and emergency contact information for health care personnel that might be involved in the subjects' subsequent medical care.

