## 1.3 Risk benefit assessment

The most common side effects of HCQ include loss of appetite, affect lability, headache, dizziness, tiredness, eye disorders, nausea and abdominal pain. Also serious side effects are possible, such as prolongation of the QT interval, torsades de pointes tachycardia, or retinopathy that might be associated with changes in the retinal pigment epithelium or visual field defects. However, the risk of retinopathy is negligible when the duration of treatment is only seven days. Because of the risk of QT prolongation and torsades de pointes tachycardia, a pre-existing long QT interval and the concomitant use of other drugs that prolong the QT interval will exclude patients from this study (see e.g. Oxiklorin Summary of Product Characteristics and Appendix 2; see also Mehra et al., 2020, and Mercurio et al., 2020).

Covid-19 is a potentially lethal viral disease, and there are no available established specific treatments against it. HCQ may have potential to modify the course of the Covid-19 disease in the early phases of the infection, so it is possible that subjects will derive direct medical benefit from their participation in the study. Reduction of the risk of hospitalization would significantly help to reduce the burden to health care systems caused by the Covid-19 pandemic, and the benefits of such a treatment would have very large societal and economic consequences.

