## 2.5 Secondary endpoints

The secondary endpoints of the study are:

- duration and severity of Covid-19-related symptoms, as reported by the participants in the form of daily self-assessments;
- number of Intensive Care Unit treatment episodes due to Covid-19 infection within four weeks of entry into the study;
- number of deaths due to Covid-19 infection within four weeks of entry into the study;
- number of hospitalizations due to Covid-19 infection within three months of entry into the study;
- number of Intensive Care Unit treatment episodes due to Covid-19 infection within three months of entry into the study;
- number of deaths due to Covid-19 infection within three months of entry into the study;
- number of treatment-related adverse events (AEs) and serious AEs (SAEs);
- number of participants with treatment-related AEs and SAEs;
- all-cause mortality within six months of entry into the study (including post-study follow-up of consenting participants);
- all-cause hospitalizations within six months of entry into the study (including post-study follow-up of consenting participants); and
- self-assessed symptoms of anxiety of the study participants, as assessed with repeated administration of the Generalized Anxiety Disorder 7-item Scale (GAD-7).

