### 3.3 General study outline

The total duration of subject participation will be approximately 3 months. The study consists of a screening period, a treatment period and a follow-up period.

At the screening visit, after a consent discussion with the investigator, the subjects will first sign the ICF and then undergo other eligibility evaluations, including collecting of a nasopharyngeal swab sample for SARS-CoV-2 PCR analysis, unless a positive PCR result is already available. Subjects will be enrolled and randomized once the results of the screening assessments are available and the investigator has confirmed the subject's eligibility. A positive test result in SARS-CoV-2 PCR analysis of a nasopharyngeal swab sample taken and analyzed outside of this study may be used for evaluation of virus positivity, if taken within five days of enrolment. Enrolment of subjects without previous PCR-confirmed SARS-CoV-2 virus shedding must have to await a positive SARS-CoV-2 PCR test result of a nasopharyngeal swab sample collected at the screening visit. The participants will be contacted by telephone as soon as the screening test results are available and told whether or not they are eligible for enrolment.

After enrolment and randomization, subjects will proceed to the treatment period. Home delivery of the medication will be arranged by the study sites, and eligible subjects are to start to use their study medication immediately upon its delivery. During the treatment period, the subjects will receive HCQ or placebo capsules twice daily during 7 days, in addition to standard care for Covid-19 infection. Daily telephone contacts by the study sites are included in the standard care protocol; also, they will be used for collection of patient-reported information. On Day 8, all subjects will be contacted by telephone for an interview on symptoms and possible AEs. Approximately 2 weeks and 4 weeks after start of drug intake, the subjects will visit their study site for assessments.

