## 6.2 Treatment period

The treatment period will last 4 weeks and the actual treatment 7 days. During the treatment period, the subjects will receive HCQ or placebo capsules twice daily with meals during 7 days. In addition, all subjects will receive standard care for their Covid-19 infection, according to local treatment practice. This includes daily telephone contacts with patients who have symptoms. The script of the daily telephone interviews includes questions on possible suicidal ideation and impairment of mental health. Should the answers to these questions reveal significant adverse changes from baseline or an elevated risk for self-harm, the investigator will be informed, and will then take the necessary actions to provide appropriate psychiatric evaluation and care for the subject, without delay. The subjects will be provided with finger-tip pulse oximetry devices and with instructions on their use during the first 14 days of the treatment period.

On Day 8, all subjects will be contacted by telephone for an interview on symptoms, concomitant medications and possible AEs.

Approximately 2 weeks and 4 weeks after start of drug intake, the subjects will visit their study site for assessments. Safety laboratory tests will be taken at these visits, as well as nasopharyngeal swab samples for SARS-CoV-2 PCR analysis and blood samples for analysis of SARS-CoV-2 antibody titres, other Covid-19-related biomarkers and HCQ concentration analysis. The GAD-7 questionnaire will be completed by the subjects. In addition, they will be asked about symptoms, concomitant medications and possible AEs that might have occurred since the last contact. At the 2-week visit, body temperature and SpO2 will also be measured, and the participant diaries will be collected.

Because of the slow elimination of HCQ, the treatment period of this study is defined as starting from the first IMP intake and ending at the 4-week visit.

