**Appendix 3: Telephone assessment form**

- 1) Yleisvointi asteikolla 0-10 (0 = huonoin mahdollinen; 10 = täysin terve verrattuna nykyistä sairautta edeltävään tilanteeseen)
- 2) Hengenahdistuksen tunne asteikolla 0-10 (0 = ei hengenahdistusta; 10 = paha hengenahdistus levossakin)
- 3) Pulssioksimetrin lukema soiton aikana mitattuna \_\_\_\_\_ ja aamulla pian heräämisen jälkeen \_\_\_\_\_
- 4) Kuumeen mittaustulos yhden desimaalin tarkkuudella aamulla heräämisen jälkeen \_\_\_\_\_
- 5) Onko muilla samassa taloudessa asuvilla saman sairauden oireita? Kenellä? Milloin ne alkoivat?
- 6) Oletteko tuntenut itsenne sekavaksi, masentuneeksi tai poikkeuksellisen jännittyneeksi viime päivien aikana?
- 7) Lääkkeen mahdolliset haittavaikutukset edellisen kyselyn jälkeen:  
\_\_\_\_\_
- 8) AE ja SAE raportointi tutkimuksesta vastaavalle lääkärille (luettelo mahdollisista haittatapahtumista alkamisaikoihin)
- 9) Muut mahdolliset oireet

Tutkittavan numero tutkimuksessa: \_\_\_\_\_

Puhelinhaastattelun päiväys ja kellonaika. Vastaukset koskevat tätä päivää:

\_\_\_\_\_

pp kk vuosi klo hh.min

Haastattelija (nimikirjoitus ja nimen selvennys):

Tutkimuskeskus(tutkimukseen osallistuva terveyskeskus):

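### The protocol gives two rules for who receives daily telephone calls; under the symptom-based rule, adverse-event enquiry during the dosing week depends on a post-randomization outcome

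*Protocol*

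**What the plan says.** Four places in the protocol describe the daily calls.

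- Synopsis, Methodology: every participant receives standard care, "which includes daily telephone contacts for evaluation of symptoms". No symptom condition is given.
- Section 3.3: "Daily telephone contacts by the study sites are included in the standard care protocol; also, they will be used for collection of patient-reported information". Again there is no symptom condition.
- Section 6.2: "This includes daily telephone contacts with patients who have symptoms".
- Section 7.3.3: outside visits, "daily telephone contact will be maintained with all subjects who have symptoms".

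The telephone form in Appendix 3 (in Finnish) collects safety data. Item 6 asks whether the subject has felt confused, depressed or unusually tense. Item 7 reads "Lääkkeen mahdolliset haittavaikutukset edellisen kyselyn jälkeen", that is, possible adverse effects of the medicine since the previous enquiry. Item 8 covers AE and SAE reporting. Sections 6.2 and 7.2.2 also place questions on suicidal ideation and mental health in the script of the daily calls.

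Section 2.5 lists as secondary endpoints the duration and severity of symptoms, the number of treatment-related AEs and SAEs, and the "number of participants with treatment-related AEs and SAEs".

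**The concern.** The two descriptions lead to different conduct. A site that follows the Synopsis and Section 3.3 would call every subject daily. A site that follows Sections 6.2 and 7.3.3 could stop calling a subject who becomes symptom-free on, say, Day 4, while that subject still has three days of capsules to take.

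Under the second rule, one post-randomization outcome (having symptoms) sets how intensively another (AEs) is measured. HCQ could act on symptom status in two opposite ways:

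- If it shortens the illness, HCQ subjects leave the daily calls sooner and are asked less often.
- If its side effects count as symptoms, HCQ subjects stay on the calls longer and are asked more often. Section 1.3 states: "The most common side effects of HCQ include loss of appetite, affect lability, headache, dizziness, tiredness, eye disorders, nausea and abdominal pain". Several of these are symptoms in the ordinary sense, and neither Section 6.2 nor Section 7.3.3 limits the word to Covid-19 symptoms.

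Blinding does not prevent either effect, because the trigger is the subject's condition and not knowledge of the allocation. At stake is the comparison of AEs between arms, which serves the secondary objective on safety and tolerability. Later analysis cannot recover answers to questions that were never asked.

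**Working it through.** **Step 1. Who is asked about AEs, and when.**

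| Contact | Who receives it | Source |
|---|---|---|
| Daily calls, dosing days 1–7 and after | All participants (no condition stated) | Synopsis, Methodology; Section 3.3 |
| The same daily calls | Subjects with symptoms | Sections 6.2, 7.3.3 |
| Day 8 call on symptoms and AEs | All | Sections 3.3, 6.2 |
| 2-week and 4-week visits, AEs since the last contact | All | Section 6.2 |
| 3-month call on AEs | All | Section 6.3 |
| Self-report of serious or significant AEs, or of worsening, during the treatment period | All | Section 7.3.3 |
| Minor AEs | Held until the next visit or call | Section 7.3.3 |

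Capsules are taken on Days 1–7, and the first contact guaranteed to every subject under Sections 6.2 and 7.3.3 is on Day 8. Within the dosing week the daily calls are therefore the only AE enquiry started by the site. The daily self-assessments in Section 7.2.2 cover symptoms, temperature and oxygen saturation; they are not an AE enquiry.

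Appendix 3 does not say which calls its form serves. Its answers refer to the day of the call, and item 7 looks back to the previous enquiry. Its mental-state item also fits the daily script described in Section 6.2. I read it as the daily form.

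**Step 2. Can a size be derived?** No. The protocol gives no rate of symptom resolution and no rate of AE detection with or without calls. It states no figure on this point that could be reproduced.

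**Step 3. Illustration, all inputs assumed.** Let s be the share of an arm on daily calls, d1 the probability of recording an AE for a subject on calls, and d0 the same for a subject not on calls. Then

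observed AE risk = true risk × [s·d1 + (1 − s)·d0].

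Assume a true risk of 0.30 in both arms, d1 = 0.90, and s = 0.70 on placebo.

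| s on HCQ | d0 | Detection, placebo | Detection, HCQ | Observed risk, placebo vs HCQ | Ratio HCQ/placebo |
|---|---|---|---|---|---|
| 0.70 | any | equal | equal | equal | 1.00 |
| 0.50 | 0.90 | 0.63 + 0.27 = 0.90 | 0.45 + 0.45 = 0.90 | 27.0 % vs 27.0 % | 1.00 |
| 0.50 | 0.80 | 0.63 + 0.24 = 0.87 | 0.45 + 0.40 = 0.85 | 26.1 % vs 25.5 % | 0.98 |
| 0.50 | 0.50 | 0.63 + 0.15 = 0.78 | 0.45 + 0.25 = 0.70 | 23.4 % vs 21.0 % | 0.90 |
| 0.35 | 0.50 | 0.63 + 0.15 = 0.78 | 0.315 + 0.325 = 0.64 | 23.4 % vs 19.2 % | 0.82 |

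If the arms are exchanged, so that side effects keep HCQ subjects on calls, the last row becomes 0.78/0.64 = 1.22. A difference needs two things together: unequal symptom status between arms, and poorer capture of AEs without the calls (d0 below d1). If either is absent, the ratio is 1.00.

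**The case against.** Several objections are sound, and they limit the point.

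**The daily calls are not the main safety net.** A reader might infer that AE collection rests on them. The documents do not say so. Every subject has the Day 8 interview directly after the course, two visits, a 3-month call and an instruction to report serious or significant AEs. A subject whose calls have ended waits at most about a week to be asked. This stands, and it reduces the problem mostly to the timing and recall of minor AEs. It does not remove it: one retrospective interview replaces several daily ones, while Section 7.3.3 asks for start and end times of each AE as far as possible, and one endpoint counts events.

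**A difference between arms is not established.** A reader might infer that the AE comparison is biased. That follows only if HCQ changes symptom status and minor AEs are captured less well without the calls. The documents show neither, and the direction is open.

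**Fewer calls are not proportionally fewer AEs.** It is tempting to count contacts under assumed symptom durations and read the shortfall as missed AEs. Later contacts ask about the whole interval since the last one, so the count does not measure detection. With 7 versus 10 symptomatic days, for example, both subjects are called on all seven dosing days, and the dosing week shows no difference.

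**The passages may differ only in detail.** All subjects have symptoms at entry (Section 4.3, criterion 3), and no explicit stopping rule for the calls is written. This is fair for the first days. It does not tell a site what to do once a subject recovers during dosing, and the natural reading of Sections 6.2 and 7.3.3 is that the calls then end.

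**Safety is summarised descriptively.** That is true, but Section 8.2.7.1 tabulates AEs by treatment group, and such a table carries unequal ascertainment as readily as a test does.

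It would also go too far to say that recurring symptoms are missed: the self-assessments in Section 7.2.2 run for two weeks without a symptom condition.

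**Conclusion.** The point holds in limited form. The protocol gives two rules for the daily calls. Under the one in Sections 6.2 and 7.3.3, the intensity of AE and mental-health enquiry during dosing depends on symptom status after randomization. Ascertainment of minor AEs can therefore differ by arm.

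The size is not derivable. Under the assumed inputs above, the ratio of observed risks runs from 1.00 to 0.82, or to 1.22 in the opposite direction, with no true difference. The outer values rest on strong assumptions: half as many subjects on calls in one arm as in the other, and only half of AEs captured without calls. Capture of serious or significant AEs should be little affected. The primary endpoint and the sample size are untouched. This should be corrected because the remedy is simple and must come before the data are collected, but it does not invalidate the trial.

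**What to change.** Reconcile the Synopsis (Methodology), Section 3.3, Section 6.2 and Section 7.3.3 to one rule for study data collection. Every randomized subject, with or without symptoms, receives the Appendix 3 form by telephone on the same fixed days in both arms, at least through Day 7, followed by the Day 8 call as already planned. State in Appendix 3 which calls the form is for. Calls made for clinical reasons beyond this schedule remain a matter for local care.

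The cost is a wording change in four places and a few short extra calls to subjects who recover before the end of dosing. The Synopsis already describes daily calls without a symptom condition, so the workload it implies does not grow.
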